| Investigational Site(s):              | Single-centre: Department of acute Medicine (DMA), Division of intensive care, Geneva University Hospital (HUG).                                                                                                                                                                                                                                                                                                                                                                                                                                                                                                                                                                                                                                                                                                                                                                                                                                        |

|                                    |                                                                                                                                                                                                                                                                                                                                                                                                                                                                                                                                                                                                                                                                                                                                                                                                                                                                                                                                                                                                                                   |
|------------------------------------|-----------------------------------------------------------------------------------------------------------------------------------------------------------------------------------------------------------------------------------------------------------------------------------------------------------------------------------------------------------------------------------------------------------------------------------------------------------------------------------------------------------------------------------------------------------------------------------------------------------------------------------------------------------------------------------------------------------------------------------------------------------------------------------------------------------------------------------------------------------------------------------------------------------------------------------------------------------------------------------------------------------------------------------|
| Statistical considerations: | 
Continuous variables will be presented according to the study group by their mean <math>\pm</math> standard deviation (SD), median, interquartile range and range. Categorical variables will be presented according to the study group by their frequencies and relative proportions. The primary outcome (time in target) will be compared between the three arms using Student t test or Mann-Whitney nonparametric test, if distributions is non-normal. For secondary outcomes, continuous variables will be compared between the three study groups using either Student t test or Mann-Whitney nonparametric test; categorical variables will be compared using either Chi-2 test, or Fischer exact test, depending on application criteria. Count data (number of hyperglycemic episodes) will be compared using Poisson regression model or negative binomial regression, if over-dispersed.
 
Significance level is set for a p-value of 0.05. All analyses will be performed using STATA IC 15.0 software.
 |
| Compliance statement:       | 
This investigation will be conducted in compliance with the CIP, the current version of the Declaration of Helsinki [1], ISO14155 [2], ICH-GCP [3] (as far as applicable) as well as all national legal and regulatory requirements.
                                                                                                                                                                                                                                                                                                                                                                                                                                                                                                                                                                                                                                                                                                                                                                                       |

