| Measurements and procedures: | 
Screening will be done every day (Monday to Friday). Eligible patients will be randomly allocated to either intervention or control group. Before inclusion, all patients will be treated according to the ICU- Geneva Protocols.
 
Collected data:
 
Baseline at study inclusion day
 
 
- Body mass, height and body mass index (BMI)
 
- Age, gender
 
- Date and time of admission in the ICU
 
- Primary diagnostic
 
- Known chronic illness (diabetes, acute kidney injury (AKI), pancreatitis, tumor, etc.).
 
- Medication influencing glycaemia (oral antidiabetics' insulin, steroids, prednisone, etc.).
 
- Renal and hepatic status
 
- Glycaemia and lactate
 
- Vitals
 
- Severity score (APACHE II, SAPS II) at ICU admission
 
 
Daily data from inclusion day (maximum follow up of 15 days)
 
When possible – Following routines measurement.
 
 
- Glucose measurements
 
- Other laboratory: lactate, CRP, sodium (Na), potassium (K), glycohemoglobin (HbA1C), urea, creatinine, glomerular filtration rate (GFR), protein, albumin, ASAT, ALAT, phosphatase alkaline, γ-glutamyltranspeptidase (GGT), bilirubin
 
- Any events (intubation, extubation, length of surgery, infusions, cardiac events, infections, requirement for red blood cell (RBC) transfusion, hemodynamic rate (HR), organ failure)
 
- Vitals (blood pressure, temperature, heart rate etc.)
 
- Antibiotics usage
 
- Vasopressor
 
- Steroids
 
- Propofol® for sedation
 
- Glucose perfusion
 
- Insulin therapy including boluses.
 
- Body weight, BMI, Ideal body weight (if needed), presence of oedema.
 
- Energy expenditure (IC or predictive formula)
 
- Energy and protein targets over the day
 
- Prescription and administration (ml of product, kcal and grams of protein).
 
- Daily water balance
 
- Diuresis
 
- Diarrhoea, constipation
 
- Nausea, Vomiting, gastric residual
 
- Physical therapy
 
- Medical Research Council Scale (MRC Scale)
 
 
Upon ICU leave
 
 
- Duration of ICU stay
 
- MRC Scale at ICU discharge
 
- Alive status at ICU discharge
 
- Duration of hospitalization
 
- Alive status at hospital discharge
 
- BMI at hospital discharge
 
 |

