### **6.2 Methods for minimising bias**

#### **6.2.1 Randomisation**

Randomization (1:1) will be stratified by the gravity score APACHE II (mild/moderate/severe) and by the diabetic status (diabetes/non diabetic patients). A randomization list using block randomization with variable blocks size 2, 4, or 6 will be computer-generated by an independent statistician.

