### 11.2 Determination of Sample Size

Based on data collected routinely at the ICU between January and March 2017, the time in target was 68% (SD 21%) for patients under the standard of care. Expecting the intervention to give an improvement of 10% of time in target, we would need 71 patients in each patient group to detect give the trial a power of 80% and an alpha error of 5% (two-sided). If the patient refuses to participate afterwards or withdraws from the study for whatever reason, they will be replaced in order to have 71 per group at the end of the study.

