#### 11.4.1 Datasets to be analysed, analysis populations

The dataset from intervention group will be analysed against both the control group and the historical control group. To assess a possible “cross-over” effect, the control group will be analysed against the historical control group. All analyses will be performed in an intention-to-treat basis: all patients will be analysed as randomized.

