#### 11.4.2 Primary Analysis

The primary outcome (time in target at the end of ICU stay) will be compared between the two groups using Student t test or Mann-Whitney nonparametric test, in case of non-normal distributions. Primary analysis will be done using linear regression with time in target as the dependent variable, the study arm as the main independent variable, and stratification variables (APACHE II categories and diabetic status) included as covariates (ref Points to consider on adjustment for baseline covariates. EMEA Agency, 2003). We will conclude superiority of the GS2 intervention, compared to the control or historical control groups, if the time in target is significantly higher ( $p < 0.05$ ).

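### The comparisons with the non-randomised historical group lack a clear adjusted analysis: the cross-over check rests on an unadjusted test, and superiority may be concluded against that group

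*Protocol*

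**What the plan says.** **Who is randomised.** Section 6.2.1: "Randomization (1:1) will be stratified by the gravity score APACHE II", and by diabetic status. This covers GS2 and control only.

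**How the historical group enters.** It consists of 71 earlier patients from the same ICU, from within two years before the trial (Sections 6.1 and 7.2.2), used without consent (Section 2.7.1). Prospective patients are screened Monday to Friday apart from the run-in phase. When several are eligible, those whose relatives can be reached come first (Section 7.2.1). Without proxy consent, a prospective patient's data are destroyed (Section 2.7.1).

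**What is compared.** Section 11.4.1 sets GS2 against both other groups. To look for cross-over, "the control group will be analysed against the historical control group". It names no test, and its statement that patients are analysed according to randomisation cannot apply to the historical group.

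**With what method.**
- Synopsis, Statistical considerations: "The primary outcome (time in target) will be compared between the three arms using Student t test or Mann-Whitney nonparametric test". No covariates are mentioned.
- Section 11.4.2: a t or Mann-Whitney sentence about two groups, then a linear regression named as the primary analysis, with "stratification variables (APACHE II categories and diabetic status) included as covariates". The paragraph ends with a rule under which superiority may be concluded against the control or the historical group at p < 0.05.

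**What is collected.** The synopsis baseline list includes age, BMI, primary diagnosis, chronic illness, medication affecting glycaemia, glycaemia and "Severity score (APACHE II, SAPS II) at ICU admission".

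**The concern.** An unadjusted two-sample test suits randomised arms. Here one group differs in calendar period and in route of entry, and the protocol itself recognises the second problem: Section 2.7.1 justifies waiving consent for historical patients because excluding those without it would cause selection bias. The prospective arms make that exclusion. Some case-mix difference is therefore foreseeable from the entry rules.

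Two conclusions depend on these comparisons. The first is the cross-over check, a main reason for having the group (Sections 3.6, 6.1 and 6.2.3). A control-against-historical difference mixes cross-over with any change in severity, diabetes or steroid use, so the check can report cross-over that did not occur or miss cross-over that did. The second is the superiority conclusion, because Section 11.4.2 admits the historical group as a comparator.

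**Working it through.** **1. The plan's own figure.** Section 11.2 gives the inputs: "the time in target was 68% (SD 21%) for patients under the standard of care", and "Expecting the intervention to give an improvement of 10% of time in target, we would need 71 patients in each patient group", with 80% power and two-sided alpha 5%.

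- Normal approximation: n = 2 × [21 × (1.96 + 0.84) / 10]² = 69.2, so 70 per group.
- t-test solution: 70.2, so 71 per group; power at 71 is 80.4%.

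The stated 71 is reproduced, and the sample size is not in question.

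**2. Precision of any comparison of 71 with 71.** SE = 21 × √(2/71) = 3.52 points, taking SD 21 in every group. The smallest significant observed difference is about 7.0 points.

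**3. Size of a case-mix shift (assumption).** The documents give none. For a binary prognostic factor, bias = difference in prevalence between periods × its effect on time in target:

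| Prevalence difference | Effect 15 points | Effect 20 points |
|---|---|---|
| 0.10 | 1.5 | 2.0 |
| 0.20 | 3.0 | 4.0 |

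**4. Effect on the unadjusted cross-over check.** With no true cross-over, the two-sided rejection probability is P(|Z + bias/3.52| > 1.96):

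| Bias (points) | Rejection rate |
|---|---|
| 0 | 5% |
| 1.5 | 7.1% |
| 2 | 8.8% |
| 3 | 13.6% |
| 4 | 20.6% |

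A shift in the other direction would offset real cross-over of the same size. If adjustment removed half of a 4-point shift, the remaining 2 points would give 8.8% instead of 20.6%, ignoring any change in SE.

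**5. Effect on the superiority rule.** Suppose that beating either comparator suffices, the tests are unadjusted and GS2 has no effect. One comparison wrongly favours GS2 with probability 2.5%. A simulation of 200,000 trials with a shared GS2 arm gave, for the either-comparator rule:

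| Shift lowering the historical mean (points) | Chance of concluding superiority |
|---|---|
| 0 | 4.6% |
| 3 | 14.6% |
| 5 | 30.1% |

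**6. Which method applies to which comparison.**

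| Comparison | Synopsis | Section 11.4.1 | Section 11.4.2 |
|---|---|---|---|
| GS2 v control | unadjusted | planned, no test named | regression, two covariates |
| GS2 v historical | unadjusted | planned, no test named | possibly the same regression, through the superiority rule |
| Control v historical | unadjusted | planned, no test named | not mentioned |

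The last row is the clearest problem: the only method stated for the cross-over check is the unadjusted one.

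**7. Gain in precision (assumption).** If baseline covariates explain 10–30% of the variance, the SE is multiplied by √(1 − R²), that is 0.95 to 0.84, a cut of 5–16%.

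**The case against.** The strongest reply is Section 11.4.2. A reader might infer from the synopsis that every historical comparison is planned as a plain unadjusted test, so that period differences will be reported as a GS2 benefit. The documents do not support that. The primary analysis is a regression, and the superiority rule in the same paragraph names the historical group, so GS2 against historical may already be adjusted. The reference to two groups stands in the t-test sentence, not in the regression sentence. Although APACHE II category and diabetes were chosen because they stratify the randomisation, as covariates they would adjust for imbalance in whichever groups enter the model. All of this stands.

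It does not reach the cross-over check, which 11.4.2 leaves out. Section 11.4.3 adds adjustment for secondary outcomes only.

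It can also be said that a covariate list for a supportive comparison belongs in the SAP. That is fair for the list. The point here is that the synopsis states an unsuitable method and conflicts with 11.4.2.

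The historical patients share the ICU and the clinical eligibility criteria, and the formal hypotheses in Section 11.1 concern the randomised arms only. This limits the damage but does not remove differences from consent, screening and calendar time.

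Finally, the shifts are assumed. A factor worth 15–20 points is 0.7 to 0.95 SD (15/21 to 20/21), and the lowest case moves the rate only from 5% to 7%. That also stands.

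**Conclusion.** The point holds in this form. The synopsis and Section 11.4.2 disagree on method and number of groups. The protocol does not make clear whether the adjusted model covers GS2 against historical, and it gives only an unadjusted test for control against historical. A case-mix difference may therefore pass for cross-over, mask it, or contribute to a superiority conclusion.

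The 7–21% rejection rates rest on assumed shifts of 1.5–4 points, SD 21 in each group and no adjustment. They illustrate the risk and do not estimate it. The superiority figures also assume that either comparator suffices. It should not be inferred that such a shift is known to exist, or that the randomised GS2-against-control comparison is compromised; that comparison remains valid. The change should be made because the check is hard to interpret as written and the remedy is cheap.

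**What to change.** Align the synopsis with Sections 11.4.1 and 11.4.2:

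1. Let the adjusted randomised comparison, GS2 against control, alone support the superiority conclusion, and remove the historical group from that rule.
2. Analyse GS2 against historical and control against historical by linear regression on group plus baseline case-mix available in both the prospective and the retrospective eCRF. Include at least APACHE II score and diabetes, and also age, BMI, diagnosis group, steroid and antidiabetic medication, and a baseline BG defined identically in all groups, such as the qualifying BG.
3. Report each adjusted difference with its 95% CI beside the unadjusted one. Label it a supportive, non-randomised estimate and state that it cannot remove calendar-time effects, since period and group membership coincide.
4. Limit the analysed-as-randomised statement to the two randomised arms.

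The cost is wording in three places and slightly more analysis. The sponsor must also check that the retrospective eCRF, whose contents the protocol does not show, holds the same fields: the synopsis defines baseline by the inclusion day, which historical patients do not have in the same sense. Sample size, randomisation and patient procedures do not change.

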## ABBREVIATIONS

|                        |                                                         |
|------------------------|---------------------------------------------------------|
| AAU             | Aalborg University                                      |
| ADE             | Adverse Device Effect                                   |
| ADO             | Oral antidiabetic drugs                                 |
| ADE             | Adverse Device Effect                                   |
| AE              | Adverse Event                                           |
| AKI             | Acute kidney injury                                     |
| ALAT            | Alanine-Aminotransferase                                |
| APACHE II score | Acute Physiology and Chronic Health Evaluation II score |
| ASR             | Annual safety report                                    |
| AUC             | Area under the curve                                    |
| ASAT            | Aspartate-Aminotransferase                              |
| BG              | Blood glucose                                           |
| BMI             | Body mass index                                         |
| BSc             | Bachelor of Science                                     |
| BW              | Body weight                                             |
| CA              | Competent Authority (e.g. Swissmedic)                   |
| CDMS            | Clinical Database Management System                     |
| CEC             | Competent Ethics Committee                              |
| CIP             | Clinical Investigation Plan                             |
| ClinO           | Ordinance on Clinical Trials in Human Research          |
| ClinO-MD        | Ordinance on Clinical Trials with Medical Devices       |
| CRF             | Case Report Form                                        |
| CRP             | C-Reactive Protein                                      |
| CRRT            | Continuous renal replacement therapy                    |
| DD              | Device deficiency                                       |
| DMA             | Department of acute medicine                            |
| DSI             | Information Systems Department                          |
| Ecrf            | Electronic case report form                             |
| EE              | Energy Expenditure                                      |
| ePDMS           | Electronic Patient Data Management System               |
| EN              | Enteral nutrition                                       |
| GCP             | Good Clinical Practice                                  |
| GFR             | Glomerular Filtration Rate                              |
| GGT             | Gamma-glutamyltransferase                               |
| GMDN            | Global Medical Device Nomenclature                      |
| GR2/GR3         | General risk 2/3                                        |
| GS2             | Glucosafe 2                                             |
| HbA1C           | Glycosylated haemoglobin                                |
| HD              | Haemodynamic                                            |

|                   |                                                                                                                                                               |
|-------------------|---------------------------------------------------------------------------------------------------------------------------------------------------------------|
| HR         | Heart rate                                                                                                                                                    |
| HRA        | Swiss Federal Human Research Act                                                                                                                              |
| HBP        | High blood pressure                                                                                                                                           |
| HUG        | Geneva University Hospitals                                                                                                                                   |
| IC         | Indirect Calorimetry                                                                                                                                          |
| ICF        | Informed consent form                                                                                                                                         |
| ICH-GCP    | International Conference on Harmonisation of technical requirements for registration of pharmaceuticals for human use – Guidelines for Good Clinical Practice |
| ICU        | Intensive care unit                                                                                                                                           |
| ID         | Identity                                                                                                                                                      |
| IFU        | Instruction for use                                                                                                                                           |
| ISO        | International Organisation for Standardisation                                                                                                                |
| IT manager | Information Technology Manager                                                                                                                                |
| IV         | Intravenous                                                                                                                                                   |
| K          | Potassium                                                                                                                                                     |
| MD         | Medical device                                                                                                                                                |
| MDR        | European Regulation on medical devices                                                                                                                        |
| Mg         | Magnesium                                                                                                                                                     |
| MRC        | Medical Research Council                                                                                                                                      |
| MSc        | Master of Science                                                                                                                                             |
| Na         | Sodium                                                                                                                                                        |
| PI         | Principal investigator                                                                                                                                        |
| PN         | Parenteral nutrition                                                                                                                                          |
| PO4        | Phosphates                                                                                                                                                    |
| RBC        | Red blood cell                                                                                                                                                |
| RDBMS      | Relational Database Management System                                                                                                                         |
| SAE        | Serious adverse event                                                                                                                                         |
| RMS        | Root Mean Square                                                                                                                                              |
| SADE       | Serious Adverse Device Effect                                                                                                                                 |
| SAPS II    | Simplified Acute Physiology Score                                                                                                                             |
| SD         | Standard deviation                                                                                                                                            |
| SIRS       | Systemic inflammatory response syndrome                                                                                                                       |
| SPN        | Supplemental parenteral nutrition                                                                                                                             |
| SVD        | Source Data Verification                                                                                                                                      |
| UIC        | Clinical investigation Unit                                                                                                                                   |
| USADE      | Unanticipated Serious Device Effect                                                                                                                           |
| WHO        | World Health Organization                                                                                                                                     |

